# Efficacy and safety of Jian-Pi Huo-Xue granule for non-alcoholic fatty liver disease: study protocol for a randomized, double-blind, placebo-controlled trial

**DOI:** 10.1186/s13063-022-06393-8

**Published:** 2022-06-02

**Keywords:** Jian-Pi Huo-Xue granule, Non-alcoholic fatty liver disease, Traditional Chinese medicine, Randomized controlled trial

## Abstract

**Background:**

Non-alcoholic fatty liver disease (NAFLD) has become the most prevalent form of chronic liver disease, with a global prevalence of 25% worldwide, but a consensus treatment is still lacking. Previous studies have shown that Jian-Pi Huo-Xue granules (JPHX) can reduce hepatic steatosis in ultrasound images, but lacked quantitative observation in imagined liver fat content. This study aimed to refine the efficacy and safety assessment of JPHX for NAFLD with magnetic resonance imaging-proton density fat fraction (MRI-PDFF) as the primary outcome.

**Methods:**

This is a randomized, double-blind, placebo-controlled clinical trial. The trial will enrol 84 NAFLD participants who will be equally randomized to receive either JPHX or a placebo for 24 weeks. Follow-up will be performed 12 weeks after the intervention. The primary outcome will be the change from baseline to week 24 in MRI-PDFF. Secondary outcomes will be the body weight, body mass index (BMI), waist circumference, waist-to-hip ratio (WHR), serum liver function, blood lipids and glucose-related indicators, quality of life measurement health survey, and traditional Chinese medicine (TCM) syndrome scale. Outcomes will be monitored at baseline, 12 weeks and 24 weeks after enrolment. Adverse events occurring in this trial will be managed and recorded promptly.

**Discussion:**

We designed a clinical trial for the treatment of NAFLD using JPHX, a TCM formulation that has been shown to have a positive effect on hepatic steatosis in a previous self-controlled trial. This trial will use a more recognized and quantitative imaging approach to demonstrate the efficacy of JPHX in the treatment of NAFLD and observe its safety to provide clinical evidence for its translational applications.

**Trial registration:**

Chinese Clinical Trial Registry ChiCTR2100046132. Registered on 4 May 2021.

## Administrative information

Note: the numbers in curly brackets in this protocol refer to SPIRIT checklist item numbers. The order of the items has been modified to group similar items (see http://www.equator-network.org/reporting-guidelines/spirit-2013-statement-defining-standard-protocol-items-for-clinical-trials/).

## Introduction

Non-alcoholic fatty liver disease (NAFLD) has become the most common form of chronic liver disorder worldwide [1, 2]. NAFLD can be histologically categorized into the nonalcoholic fatty liver (NAFL) or nonalcoholic steatohepatitis (NASH) [3]. NAFL is histologically characterized by hepatic steatosis over 5% without evidence of hepatocellular injury. Histologically, NASH is characterized by hepatic steatosis over 5% with hepatocyte ballooning degeneration and inflammation, with or without fibrosis [4]. The prevalence of NAFLD is increasing year by year, an estimated 25% of the global population has NAFLD [5, 6]. The incidence of NASH is projected to increase by up to 56% in 2030 [7], and NASH is predicted to be the main cause of hepatocellular carcinoma in liver transplants [2, 8]. China experienced an unexpected rapid increase in the burden of NAFLD over a short period [9]. According to the epidemiological survey in China, the prevalence of NAFLD in the overall population is 29.6% [10]. Patients with NAFLD have occult onset and chronic progression of liver disorders that are usually associated with metabolic syndrome, including obesity, abnormal lipid metabolism, hypertension diabetes, and insulin resistance [11–13]. An international expert consensus has reached the concept of metabolic associated fatty liver disease (MAFLD) to reflect the hepatic manifestations of multisystem disorder [14–16].

The prevalence of NAFLD is associated with sedentary behaviour, low physical activity, and poor diet lifestyle, lifestyle modifications such as diet and exercise are recommended as the primary intervention for NAFLD [2]. However, lifestyle interventions can be useful but hard for effective long-term maintenance. Current therapeutic landscape for NAFLD mainly focuses on interventions in energy intake, energy processing, lipotoxic liver injury, and inflammation and fibrosis leading to cirrhosis. However, all drugs are still in preclinical development or clinical trials to evaluate efficacy [17], and there are currently no FDA-approved drugs for NAFLD.

The prevention and treatment of chronic liver disease by traditional Chinese medicine (TCM) have a long history and extensive clinical application in China. Jian-Pi Huo-Xue granules (JPHX) consists of 8 herbs and is a TCM experience formula for the treatment of alcoholic liver disease (ALD) and NAFLD [18, 19]. Our previous experiments showed that JPHX attenuates intestinal mucosal epithelial cell injury, decreases intestinal endotoxin leakage [20–22], and ameliorates hepatic steatosis and inflammation [23, 24] in ALD rats induced by a Lieber-DeCarli liquid diet. JPHX also has a hepatoprotective effect in NAFLD rats fed a methionine-choline-deficient diet [25]. “Leaky gut” is a common pathological feature of ALD and NALFD; the intestinal barrier protection of JPHX in ALD rats also suggests a potential therapeutic effect on NAFLD.

In a previous self-controlled pilot study, He et al. treated NAFLD patients with JPHX and found that JPHX significantly improved imaged liver fat assessed by ultrasound and reduced liver dysfunction [26, 27]. However, the pilot study lacks quantitative observations of the primary efficacy outcome. Therefore, we designed a randomized, double-blind, placebo-controlled trial to investigate the clinical efficacy and safety of JPHX as a treatment for NAFLD using magnetic resonance imaging-based proton density fat fraction (MRI-PDFF) as the primary outcome.

## Methods

### Study design

This is a randomized, double-blind, placebo-controlled clinical trial. The flow chart of the trial is shown in Fig. 1. This trial is conducted in Shuguang Hospital Affiliated with Shanghai University of Traditional Chinese Medicine.

**Fig. 1 Fig1:**
[figure not shown]
Flow chart of this trial

### Interventions

Participants who met the inclusion criteria and signed an informed consent form will be randomly assigned to the JPXH group or the placebo-controlled group.

JPHX group: JPHX granules (6.39 g/pack × 2 packs, bid)

Placebo group: JPHX-placebo granules (2 packs, bid)

JPHX granules and placebo are recommended to be diluted in water and taken half an hour after meals. JPHX granules are composed of 8 kinds of Chinese herbs, including *Atractylodes macrocephala Koidz.* (Bai Zhu), *Salvia miltiorrhiza Bge.* (Dan Shen), *Citrus aurantium L.* (Zhi Qiao), *Paeonia lactiflora Pall.* (Bai Shao), *Pueraria lobata (Willd.) Ohwi* (Ge Gen), *Alisma orientalis (Sam.) Juzep.* (Ze Xie), *Schisandrae Chinensis Fructus.* (Wu Wei Zi), and *Curcuma Longa L.* (Jiang Huang) [19]. The placebo granules will be masked with the same packaging and similar taste compared to JPHX. Both JPHX and placebo are manufactured and packaged by Jiangyin Tianjiang Pharm Co., Ltd, Jiangyin city, Jiangsu, China.

Participants will receive regular health education, including diet control, exercise, and behaviour modification. ① Diet adjustment: diets with low-sugar, low-fat, and high-vitamin are recommended. ② Strengthen physical exercise: moderate-equivalent-intensity exercise, more than 30 min each time, 4 times a week. ③ Adjust mood and maintain a good mood; ④ During the trial, other TCM herbs and Western medicines mainly used to lower lipids or treat liver damage are prohibited.

### Withdrawal, dropout, and discontinuation

Participants will be advised to discontinue participation in the event of a serious adverse event (SAE), or a condition during the course that does not meet the requirements of this trial, such as pregnancy or taking illicit drugs. There are no special criteria for modifying allocated interventions. Participants are free to withdraw at any time and the reason for withdrawal will be investigated. The reason and its connection with this trial will be recorded after investigation. If a moderate or severe adverse reaction determined to be related to the clinical trial occurs in more than 25% of the total participants, or if the required number of participants is not fully enrolled within the schedule, this clinical trial may be terminated.

### Strategies to improve adherence to interventions

Investigators will conduct regular phone calls or connect participants via communication software to ensure compliance. We will evaluate the compliance to the treatment by granules packet count, patients who complete 80% of the recommended treatment will be considered in compliance.

### Post-trial care

Patients that are enrolled into the trial are covered by indemnity for negligent harm in accordance with national laws and regulations. If the participant has the treatment and examination required for other diseases at the same time, it will not be included in the free scope.

### Outcomes

The primary outcome is the relative change of MRI-PDFF from baseline to 24 weeks.

The secondary outcomes include changes in ① body weight, body mass index (BMI), waist-to-hip ratio (WHR); ② serum liver function including total bilirubin (TBIL), direct bilirubin (DBIL), indirect bilirubin (IDBIL), ALT, aspartate aminotransferase (AST) [16], gamma-glutamyl transpeptidase (GGT), alkaline phosphatase (ALP), albumin (ALB) [28], pre-albumin (Pre-ALB), and total bile acid (TBA); ③ fasting serum lipids; ④ blood glucose-related indicators, such as fasting plasma glucose (FPG), fasting insulin (FINS), and Homeostasis model assessment – insulin resistance (HOMA-IR). All mentioned serum biochemical markers will be measured at baseline, 12 weeks and 24 weeks after randomization. ⑤ Health related quality of life (SF-36). ⑥ Chronic Liver Disease Questionnaire (CLDQ), ⑦ TCM Syndrome Score Scale (TCMSSS).

Blood routine, urine routine, blood urea nitrogen, creatinine, uric acid, and SAEs are included as safety outcomes in this trial.

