#### Exclusion criteria

We will exclude those who: ① regularly took other hepatoprotective drugs within 1 month before screening; ② have taken drugs that may affect lipid metabolism within 3 months before screening, such as tamoxifen, amiodarone, sodium valproate, methotrexate, and glucocorticoid; ③ combined with special conditions that may lead to fatty liver, such as total parenteral nutrition, inflammatory bowel disease, celiac disease, hypothyroidism, Cushing’s syndrome, β-lipoprotein deficiency, lipoatrophic diabetes, and Mauriac syndrome; ④ are diagnosed of ALD (male alcohol intake > 30g/day, female alcohol intake > 20g/day), liver cirrhosis, liver decompensation, and other chronic liver diseases, such as hepatitis B, hepatitis C, autoimmune liver diseases; ⑤ have received liver transplantation; ⑥ combined with unstable controlled type 2 diabetes (HbA1c≥9.5% before enrolment); ⑦ combined with a high or extremely high risk of arteriosclerotic cardiovascular disease (ASCVD); ⑧ have had bariatric surgery in the past year or have taken weight-loss drugs in the past three months, and have lost more than 10% of their body weight; ⑨ have a history of drug or narcotic abuse; or ⑩ are pregnant and lactating or have major primary diseases or malignant tumours.

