### Study visit overview

Five visits including one follow-up are designed in this trial: at 6, 12, 18, 24, and 36 weeks after enrolment. Each time point has 5 days of time flexibility. Participants will have their vital signs checked at each visit, receive health education and medication for the next 6 weeks, and return any remaining drugs from the previous visit. Other concomitant medications and their doses during this period will be recorded in the CRF. Compliance with the treatment will be evaluated by pack count at each visit and serious adverse events will be recorded. MRI-PDFF examinations will be performed at weeks 0 and 24, and laboratory indicators will be measured at weeks 0, 12, and 24. SF-36, CLDQ, and TCMSSS will be filled out at 0 and 24 weeks. The TCMSSS consists of 55 questions about conventional symptoms of TCM syndromes, and each symptom is divided into four grades according to its frequency or degree. These questions are derived from a Patient-Reported Outcome (PRO) questionnaire for patients with hepatitis B virus-related cirrhosis (PHBC-PRO) [33, 34] and are expanded to studies of TCM for the treatment of chronic liver diseases. TCM syndrome diagnosis and its related degree can be reflected according to the combination and degree of positive symptoms. Any questions raised by participants will be answered to facilitate completion. The study schedule is shown in Fig. 2.

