### Statistical analysis

Statistical analysis will be performed by an independent researcher. The primary outcome efficacy evaluation will be conducted in the full analysis set [35] according to the intention-to-treatment (ITT) principle. Cases that met the trial protocol had good compliance (> 80%), did not take illicit drugs during the trial, and completed the contents of the CRF regulations will be defined as the Per-Protocol Set. The missing data will be replaced using the last observation carried forward (LOCF) method.

Continuous data will be described using mean ± standard deviation or median (range) depending on the distribution of the data. Comparison of mean or median values of continuous variables from the two groups will be undertaken using an independent *t* test or Wilcoxon rank-sum test. Paired *t* test or Wilcoxon signed-rank test will be used to compare the distribution of pre- and post-treatment changes within each group. Categorical data will be described by frequency counts and constituent ratio and will be compared using the chi-square test/Fisher exact test. All statistical analyses will be conducted with the bilateral test, and *P* value less than or equal to 0.05 will be considered statistically significant. Subgroup analyses will be performed based on information collected to explore the source of potential high heterogeneity.

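### Fasting insulin and HOMA-IR are outcomes for everyone, although patients on injected insulin can enter and HOMA-IR does not measure insulin resistance in them

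*Protocol article*

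**What the plan says.** All references are to the protocol article.

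- **Outcomes.** The secondary outcomes include "blood glucose-related indicators, such as fasting plasma glucose (FPG), fasting insulin (FINS), and Homeostasis model assessment", the last being HOMA-IR. On timing: "All mentioned serum biochemical markers will be measured at baseline, 12 weeks and 24 weeks after randomization". No subset of participants is named.
- **Exclusion criteria.** The one criterion on glycaemic control reads "combined with unstable controlled type 2 diabetes (HbA1c≥9.5% before enrolment". Type 2 diabetes below that level is therefore eligible, unless another criterion applies.
- **Interventions.** During the trial, "other TCM herbs and Western medicines mainly used to lower lipids or treat liver damage are prohibited". Insulin and other glucose-lowering drugs are not named.
- **Study visit overview.** "Other concomitant medications and their doses during this period will be recorded in the CRF". The article states no analysis that uses this record.
- **Statistical analysis.** "Comparison of mean or median values of continuous variables from the two groups will be undertaken" with an independent t test or a Wilcoxon rank-sum test. Subgroup analyses are announced in general terms, and neither diabetes nor insulin use is mentioned.

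**The concern.** HOMA-IR multiplies fasting glucose by fasting insulin and reads the product as resistance to the patient's own insulin. If insulin is injected, the assay result is no longer only the patient's own secretion. The number can still be calculated, but it does not mean what its name says. A dose change can then move it with no change in insulin resistance.

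The case is not remote. The Introduction itself says that NAFLD usually comes with metabolic disorders, including diabetes and insulin resistance. An exclusion threshold at HbA1c 9.5% also makes sense only if some diabetic patients below it are expected to enrol.

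What is at stake is the reading of two secondary outcomes. A difference in HOMA-IR could not be cleanly called a difference in insulin resistance, and a real difference could be diluted. Starting or changing any glucose-lowering drug during the 24 weeks would also move fasting glucose, fasting insulin and HOMA-IR independently of the granules.

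**Working it through.** **1. What the stated rules allow together.**

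| Question | Answer in the article | Section |
|---|---|---|
| Can a patient with type 2 diabetes enter? | Yes, below HbA1c 9.5% | Exclusion criteria |
| Is prior insulin an exclusion? | Not named | Exclusion criteria |
| Is insulin prohibited during the trial? | Not named | Interventions |
| Is a stable dose of glucose-lowering drugs required? | No such condition stated | whole article |
| Who contributes to fasting insulin and HOMA-IR? | No limit stated | Outcomes |
| Does the analysis separate insulin users? | No | Statistical analysis |

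Values taken under injected insulin can therefore enter the comparison.

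**2. Arm sizes.** The article gives no figure for HOMA-IR. Its arm sizes come from the primary outcome (Sample size justification). With the formula as printed, z(0.95) = 1.645 and z(0.80) = 0.842:

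(1.645 + 0.842)² × (0.6 × 0.4 + 0.3 × 0.7) / (0.30 − 0.01)² = 33.08, stated as 33. For dropout, 33 / 0.8 = 41.25, stated as 42 per arm, 84 in total. These serve here only as denominators.

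**3. Dilution.** The share f of insulin users is not in the article, so a range is assumed. If HOMA-IR carries no treatment signal in users and the SD is unchanged, the mean difference is multiplied by (1 − f). The total n for the same power rises by 1/(1 − f)². If users are left out instead, the effect is undiluted and the total to enrol rises only by 1/(1 − f).

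| f (assumed) | Users among 84 | Effect retained | n factor, users kept | n factor, users left out |
|---|---|---|---|---|
| 5% | 4.2 | 95% | 1.11 | 1.05 |
| 10% | 8.4 | 90% | 1.23 | 1.11 |
| 20% | 16.8 | 80% | 1.56 | 1.25 |
| 30% | 25.2 | 70% | 2.04 | 1.43 |

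On these assumptions, leaving users out costs less power than keeping them in.

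**4. What one patient can do (all values assumed).** Take HOMA-IR = glucose (mmol/L) × insulin (mU/L) / 22.5; the article does not print the formula.

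- Before: 8 × 15 / 22.5 = 5.33.
- After starting insulin: 7 × 60 / 22.5 = 18.67.
- Change: +13.33.
- Shift in the mean change of an arm of 33: 13.33 / 33 = 0.40 for one such patient, 3 × 13.33 / 33 = 1.21 for three.

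These shifts apply to a comparison of means with every affected patient in one arm. Equal numbers in both arms with the same change would cancel in the difference and leave only added variance. Under the rank test, one of 33 patients moving from the middle to the top rank changes P(X > Y) by at most about 0.5 / 33 = 0.015.

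**The case against.** **The affected group may be small or absent.** Other criteria could remove diabetic patients: "combined with a high or extremely high risk of arteriosclerotic cardiovascular disease (ASCVD" is an exclusion whose risk categories the article does not define. So is "have taken drugs that may affect lipid metabolism within 3 months before screening, such as tamoxifen, amiodarone, sodium valproate, methotrexate, and glucocorticoid", an open list, although its examples include no glucose-lowering drug. This stands in part: the article neither shows nor rules out that insulin users will enrol. A reader might infer that some of the sample certainly yields invalid values, and the text does not support that.

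**Randomisation and blinding protect the comparison.** Largely right. Insulin use at baseline is balanced in expectation, so the main effect is noise. A reader might infer from the 0.40 and 1.21 shifts that the trial will report a spurious effect on insulin resistance. Those figures need a test on means, invented laboratory values and all affected patients in one arm. The article allows a rank test when the distribution calls for it, and that limits outliers. It does not make the index valid in an insulin user. Nor does randomisation prevent drug changes afterwards from differing by arm.

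**This is detail for the analysis plan.** The article assigns the full analysis set only to the primary outcome, so it does not say outright that every HOMA-IR value will be pooled. An unseen analysis plan may deal with it. The point remains because eligibility, permitted drugs and outcome definitions are all stated here, and their combination creates the problem.

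**Excluding insulin users over the whole trial would itself bias the comparison.** Correct. If the granules affect glycaemia, starting insulin may depend on the arm, so a restriction on use at weeks 12 and 24 conditions on events after randomisation. The main restriction should therefore rest on baseline use alone.

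**Fasting glucose is a valid measurement whatever the drug.** Also correct. A drug change alters how its change is interpreted, but the measurement itself does not fail. The same holds for changes in oral drugs: they confound the change scores without invalidating the index.

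**Conclusion.** The point holds as a limited one. As written, the plan can include fasting insulin and HOMA-IR values taken under injected insulin, and in those participants HOMA-IR does not measure insulin resistance. The consequence is mainly added noise and an unclear reading of two secondary outcomes, with possible bias if insulin or other glucose-lowering treatment changes differently by arm after randomisation.

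The size depends on a share that the article does not give. Over an assumed 5% to 30%, the retained effect is 95% to 70%, given no signal in users and an unchanged SD. The MRI-PDFF primary outcome, the sample size and the safety outcomes are not touched. The change is worth making because it is cheap and the data it needs are already to be collected.

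**What to change.** In Outcomes and Statistical analysis, before unblinding:

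1. State that the between-group analysis of fasting insulin and HOMA-IR is restricted to participants not using exogenous insulin at baseline. This is a pre-randomisation characteristic, so the comparison stays randomised.
2. Report by arm the number who start insulin or change a glucose-lowering drug after randomisation, from the medication record described in Study visit overview.
3. Add a sensitivity analysis of fasting glucose, fasting insulin and HOMA-IR without values taken after such a change, labelled as conditioning on post-randomisation events. Say whether the removed values are left missing or filled by the last-observation rule that the article applies to missing data.
4. Keep fasting glucose analysed in all participants, with item 3 as sensitivity only.

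The cost is a few sentences and a few fewer participants in fasting insulin and HOMA-IR. The baseline restriction does not remove people who start insulin later; items 2 and 3 show how much that matters. No new data collection is needed, and no rule on glucose-lowering treatment itself is proposed.

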### Sample size justification

A previous pilot trial in Shuguang Hospital used comprehensive scores of abdominal ultrasounds to evaluate efficacy. The score includes the evaluation of 7 indicators such as liver shape, contour, echo, and vascular structure. Each indicator is divided into 4 grades: normal, mild, moderate, and severely abnormal. Twenty-six patients (65%) experienced a 1-grade or more decrease in at least 3 indicators after treatment with JPHX compared to baseline [27, 29]. In this trial, a 26% relative reduction from baseline in liver MRI-PDFF will be expected in 60% of JPHX-treated cases compared to 30% in the placebo control group. Assuming *α* = 0.05, *β* = 0.2, *π*_*T*_ = 0.6, *π*_*C*_ = 0.3, *δ* = 0.01, *n*_*T*_ : *n*_*C*_ = 1:1. According to the optimal sample size calculation formula, each group will get 33 samples. Considering the dropout rate of 20%, a minimum of 42 individuals will be obtained per group.$${\mathrm{n}}_{\mathrm{T}}={\mathrm{n}}_{\mathrm{C}}=\frac{{\left({z}_{1-\alpha }+{z}_{1-\beta}\right)}^2\left[{\pi}_T\left(1-{\pi}_T\right)+{\pi}_C\left(1-{\pi}_C\right)\right]}{{\left[\left({\pi}_T-{\pi}_C\right)-\delta \right]}^2}$$

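### Apart from laboratory tests, the safety outcomes and the visit record name only serious adverse events, which is narrower than the abstract and than the termination rule requires

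*Protocol article*

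**What the plan says.** Four places in the protocol article bear on which adverse events count.

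- **Outcomes** (safety outcomes): "Blood routine, urine routine, blood urea nitrogen, creatinine, uric acid, and SAEs are included as safety outcomes in this trial". The list holds laboratory measurements and one class of clinical event, SAEs.
- **Study visit overview** (visit record): "Compliance with the treatment will be evaluated by pack count at each visit and serious adverse events will be recorded". No other class of adverse event is mentioned there. The same section sets the visits: "Five visits including one follow-up are designed in this trial: at 6, 12, 18, 24, and 36 weeks after enrolment".
- **Abstract, Methods**: "Adverse events occurring in this trial will be managed and recorded promptly". This is not limited to serious events.
- **Withdrawal, dropout, and discontinuation** (trial-level rule): "If a moderate or severe adverse reaction determined to be related to the clinical trial occurs in more than 25% of the total participants", the trial may be terminated. The same section gives SAEs a separate role, as a reason to advise the individual participant to stop.

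**The concern.** Safety is in the trial's title, in the aim stated in the abstract and in the conclusion of the Discussion. The placebo arm lets reactions be compared between JPHX and control, but only for events that are defined as outcomes and collected in both arms.

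Two Methods sections independently limit the clinical events to SAEs. The abstract and the termination rule both presuppose something wider. The rule works on severity (moderate or severe) and relatedness. Seriousness is a different attribute, and a reaction can be moderate, or even severe, without being serious.

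Two things are at stake:

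1. If the outcome list is followed literally, non-serious reactions are not a safety outcome and need not be reported by arm.
2. If the visit description is followed literally, those overseeing the trial would not have, from that record alone, the count on which the termination rule depends.

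**Working it through.** **Inputs**

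- Planned total: 84, randomized 1:1 (Abstract, Methods).
- Size per group: "each group will get 33 samples" before dropout, then "Considering the dropout rate of 20%, a minimum of 42 individuals will be obtained per group" (Sample size justification).
- Termination threshold: more than 25% of all participants (Withdrawal, dropout, and discontinuation).

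**Step 1. Reproduce the denominator.** 33 / (1 − 0.20) = 41.25, rounded up to 42 per group; 2 × 42 = 84. This agrees with the abstract. The sample size is used here only as the denominator of the rule.

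**Step 2. Turn the threshold into a count.** 0.25 × 84 = 21. The rule says more than 25%, so it is met at 22 participants: 22/84 = 26.2%, whereas 21/84 = 25.0% does not meet it.

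**Step 3. Compare what the rule needs with what each section provides.**

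| Section | Events covered | Severity and relatedness | Enough for the rule? |
|---|---|---|---|
| Outcomes | Laboratory tests, SAEs | Not mentioned | No |
| Study visit overview | SAEs | Not mentioned | No |
| Abstract, Methods | Adverse events in general | Not mentioned | Events yes; grading not stated |
| Withdrawal, dropout, and discontinuation | Related moderate or severe reactions | Presupposed | This is the rule itself |

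**Step 4. How far an SAE record can differ from the count.** Take exactly 22 participants with a related moderate or severe reaction and consider those reactions only. If none is serious, the SAE record shows 0 when the rule is met. If all are serious, it shows 22. The record is therefore compatible with any value from 0 to 22 and does not determine whether the threshold has been passed. No event rate is assumed.

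**The case against.** **The abstract already promises that all adverse events are recorded, and neither Methods section says that only SAEs are.** This is the strongest point, and part of it stands. A reader might infer that the trial will not collect non-serious events, or that the termination rule cannot be applied at all. The documents support neither. The abstract's sentence is general, and the rule itself presupposes that someone grades and attributes reactions. What remains is that the outcome list and visit description, as printed, are narrower than both. Moreover, recording an event does not make it a safety outcome reported by arm.

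**An article condenses; the adverse event form and its grading belong in the full protocol or CRF.** This is fair as far as missing detail goes, and the CRF and the study schedule figure are not available here. But the article does address both safety outcomes and visit recording, and what it states disagrees with its own abstract and its own termination rule. The point rests on that disagreement.

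**SAE may be loose wording for any adverse event.** This is unlikely. The visit description spells the term out in full, and the withdrawal section uses SAEs and moderate or severe reactions for two different actions.

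**Laboratory tests also cover safety.** They do, and a reader who took the list to contain nothing but SAEs would be wrong. Laboratory values do not, however, give graded and causally assessed clinical reactions.

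**Conclusion.** The point holds as an internal inconsistency with practical consequences for safety reporting. The Outcomes section and the Study visit overview name SAEs as the only clinical events, while the abstract and the termination rule require more. Followed as written, those two sections omit non-serious reactions from the by-arm safety outcomes and describe a visit record that does not by itself yield the count for the rule.

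The threshold is at least 22 of 84 participants, assuming full enrolment and that the total means everyone enrolled. The rule permits termination and does not compel it. How many non-serious reactions would go unreported cannot be estimated from the documents, and whether the unseen CRF already captures them is unknown. The primary efficacy analysis is not affected. The change should be made, because it is cheap and touches a stated aim and a termination rule.

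**What to change.** Amend two sentences.

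1. In Outcomes, make all adverse events a safety outcome reported by arm, with SAEs as a subset, alongside the laboratory tests already listed.
2. In Study visit overview, state that all adverse events are recorded at every visit (weeks 6, 12, 18, 24 and 36), each with its severity, seriousness and relatedness.

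Both sections would then agree with the abstract, and the visit record would supply what the termination rule needs. The cost is the wording change, plus slightly more CRF recording if non-serious events are not already captured. No extra visit or blood draw is needed.
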